**Facility level (n=8)**									
	TG-DSD^a^ sites	4 (50)		Checklists		Quantitative survey		KIIs^b^ (6/site, n=24)	
	SSD^c^ sites	4 (50)		Checklists		Quantitative survey		KIIs (6/site, n=24)	
**Transgender people** **living with HIV (n=400)**									
	Care at TG-DSD sites	200 (50)		HIV RNA level		Quantitative survey		IDI^d^ (n=15)	
	Care at SSD sites	200 (50)		HIV RNA level		Quantitative survey		IDI (n=15)	
**Transgender people** **without HIV (n=200)**									
	Care at TG-DSD sites	100 (50)		Tenofovir-level		Quantitative survey		IDI (n=15)	
	Care at SSD sites	100 (50)		Tenofovir-level		Quantitative survey		IDI (n=15)	

^a^TG-DSD: transgender-specific differentiated service delivery.

^b^KII: key informant interview.

^c^SSD: standard service delivery.

^d^IDI: in-depth interview.

To meet the third aim, we will estimate the incremental costs of DSD implementation compared with SSD from the provider perspective by conducting a bottom-up analysis of the resources used and costs accrued by the TG-DSD cohort and comparing them to the costs of SSD established in recent studies [53,54]. We will also calculate the cost per successful outcome (suppressed viral load for those on ART and prevention-effective adherence for those without HIV) and the total budget required for a national roll out of TG-DSD.

### Ethical Considerations

Ethics approval was received for this study from the University of Witwatersrand Human Research Ethics Committee (M220420) in June 2022 and from the Duke University Health System institutional review board (Pro00113320) in June 2023. All participants complete a written informed consent process, including the option to opt-out of participation, after eligibility screening and before any data collection activities. All data are collected in a private room at the study site or a private area (eg, mobile van) in the community. Name and contact information are collected in order to send reminders of follow-up study visits. However, personal identifiers are retained separate from study data. Each participant is assigned a unique anonymous study identifier that is associated with their data. Personal identifiers are only accessible by specific study staff who have permission to contact participants for reminder purposes. All study staff have been trained in human subjects protections and good clinical practices. Participants receive ZAR 300 (US $17) at the end of each study visit as well as light refreshments (eg, a sandwich).

### Study Frameworks

This study uses the Reach, Effectiveness, Adoption, Implementation, and Maintenance (RE-AIM) [55,56] implementation science evaluation framework and the gender affirmation framework [57]. Data collection and analysis for all aims are guided by RE-AIM. Key measures and analyses for aim 2 are also guided by the gender affirmation framework, a conceptual framework that outlines mechanisms by which TG-DSD is expected to improve HIV outcomes.

RE-AIM is often used to guide the evaluation of implementation strategies [55]. It is well-suited for studies of projects that are in the implementation process [56] and guides our selection of study measures [58]. The first 4 RE-AIM domains are listed in Textbox 2, with examples of research questions for each domain. These domains (reach, effectiveness, adoption, and implementation) are most applicable to this study, while the fifth domain, maintenance, will not be addressed.

Reach, Effectiveness, Adoption, Implementation, and Maintenance (RE-AIM) domains applied in this study and example research questions.
**Domains and example research questions**
Reach: Is the intervention reaching the desired population?Effectiveness: Does the intervention accomplish its goals?Adoption: To what extent are the people who should deliver the intervention participating?Implementation: To what extent is the intervention consistently implemented?

The gender affirmation framework provides a model for drivers of HIV outcomes. Gender affirmation is a process of recognition and support for one’s gender identity [57]. Gender affirmation has 4 core facets: medical (eg, GAHT and surgery), psychological (eg, self-acceptance and sense of alignment with one’s gender), social (eg, use of desired name and pronouns and wearing clothes associated with one’s gender identity), and legal (eg, change of name and gender marker on legal documents) [59].

The gender affirmation framework posits that antitransgender stigma leads to social oppression and psychological distress. Social oppression reduces access to gender affirmation while psychological distress increases the need for gender affirmation. The gap between access and need drives behaviors that increase HIV vulnerability. Significant relationships between unmet gender affirmation needs and HIV risk behavior as well as ART interruptions are well documented [57,60-63]. This framework informs our hypothesis that TG-DSD will reduce stigma and increase gender affirmation, thereby increasing engagement in HIV services and improving HIV outcomes (ie, viral suppression and prevention-effective adherence) among transgender people. Our measures of stigma as well as medical (ie, GAHT) and psychological gender affirmation will be used to test hypothesis 3 for aim 2.

### Transgender-Specific DSD Models

Wits RHI provides TG-DSD models at 4 sites. Of these, 2 (50%) are stand-alone sites and 2 (50%) are in park homes on an SSD facility campus. All TG-DSD sites offer GAHT in an integrated HIV and primary care package, which includes both facility-based (fixed) services and community-based (mobile) services. All services are free to clients.

Details of the care provided at those sites have been published elsewhere [49], and an overview is provided in Table 2 and Textbox 3. Each site employs peer navigators, community liaison officers, professional nurses, a social worker, a site manager, and community health workers. Each site also employs a sessional physician and psychologist. Services have been designed and delivered in collaboration with local transgender community–based organizations. All cadres of staff (clinical, nonclinical, professional, and lay) complete transgender sensitization training conducted by transgender-led community organizations. These trainings build staff skills in providing nonstigmatizing, transgender-friendly services. Trainings take place upon hire and routinely thereafter during in-service sessions.

**Table 2 table2:** Wits RHI transgender-specific differentiated service delivery and models of care in South Africa.

	Guateng	Cape Town	Nelson Mandela Bay	Buffalo City
Model	Stand-alone	Stand-alone	Colocated with SSD^a^	Colocated with SSD
Population density	Urban	Urban	Peri-urban and rural	Peri-urban and rural
GAHT^b^	Provided on site	Provided on site	Provided on site	Provided off site

^a^SSD: standard service delivery.

^b^GAHT: gender-affirming hormone therapy.

Components of Wits RHI transgender-specific differentiated service and their descriptions.
**Service and description**
Clinical services: primary health care, sexually transmitted infection screening and treatment, tuberculosis screening, HIV treatment and prevention, and gender-affirming hormone therapy (GAHT)Ancillary services: psychosocial support, referral to postviolence care, legal support, and substance use servicesFull-time staff: 4 to 10 peer navigators, 0 to 2 community liaison officers, 1 social worker, 0 to 2 community health workers, 2 nurses, and 1 site managerSessional staff: 1 physician and 1 psychologistCommunity partnerships: local transgender community organizations and local AIDS councilsCommunity leadership: community advisory boards comprising transgender advocates and activists who guide and monitor services

Where possible, transgender people are appointed in all staff cadres. Most community health workers and peer navigators are transgender people. Program-specific Facebook (Meta Platforms, Inc) and WhatsApp (Meta Platforms, Inc) groups provide information on services and events to the community. Transgender-friendly health information, education, and communications printed materials are available.

Clinical services related to GAHT are provided only at the facility. The client comes to the facility monthly for the first 3 months on hormones for laboratory testing, side effect assessment, and dose adjustments. After the third month, when clients are on a stable dose, they return to see the medical provider at month 6, then every 6 months subsequently for monitoring. Multi-month dispensing of hormones is currently a challenge in South Africa due to stock shortages; therefore, clients on GAHT return monthly for dispensing visits only.

In addition to facility-based GAHT and HIV services, each TG-DSD site provides mobile HIV services in the community throughout their catchment area. These mobile services are offered in a van equipped with examination rooms and basic medical equipment. Mobile teams include a peer navigator, a community health worker, and a professional nurse. They offer primary health services, HIV testing and counseling, and multi-month dispensing of ART and PrEP.

### SSD Models

Public primary health care centers in South Africa provide SSD through a professional nurse-based, physician-supported infrastructure of >3500 clinics and community health centers, available within 5 km of more than 90% of the population and free at the point of care [64]. Primary health care centers are the first point of entry for health care access. These facilities provide a comprehensive package of basic services, including maternal, child, and reproductive health, and HIV and tuberculosis testing and treatment, including ART, screening and care for noncommunicable diseases, and treatment of common ailments. The primary health care system is supported by community teams, referred to as ward-based primary health care outreach teams. These teams are allocated to specific wards according to the size, geography, and social and structural considerations. They provide health information to the community, and screen and refer those who need further management to corresponding primary health care facilities [65]. Despite a progressive constitutional and legal framework, transgender people continue to face stigma and discrimination when they access SSD sites for health care [66-68]. GAHT is not available in public primary health care facilities. In general, access to GAHT is limited in South Africa, where it is only provided by specialist endocrinologists at tertiary facilities; and transgender people may face waiting times of up to 20 years or more to access gender-affirming surgery in the public sector [69,70].

### Study Procedures

#### Facility-Level Eligibility, Recruitment, and Data Collection

We have enrolled all 4 Wits RHI TG-DSD sites listed in Table 2. In collaboration with district health departments, we have recruited 1 SSD site within the catchment area of each DSD site for a total of 4 TG-DSD sites and 4 SSD sites. SSD sites are similar to TG-DSD sites in urbanicity, socioeconomic status of the client population, and types of HIV services offered (ie, both ART and PrEP). We shared information about the study with the district and SSD site leadership and invited them to participate in the study. Study staff will visit all 8 recruited sites (TG-DSD and SSD) to complete a standardized observation checklist at baseline and 12 months. Checklist items include the number, type, and role of staff; content and frequency of staff training; facility hours, amenities (eg, number of rooms), and community outreach efforts; standard policies and procedures for delivery of HIV and sexually transmitted infection testing, PrEP, ART, and GAHT services, including, but not limited to counseling, prescribing, dispensing, laboratory monitoring, tracking, and visit frequency; sex and gender documentation on clinical forms and records; the number of transgender clients; number of transgender people prescribed GAHT; number of transgender people prescribed PrEP; number of transgender people prescribed ART; availability and use of psychosocial services; and cost of service delivery.

Leadership at each recruited site facilitate recruitment of 6 staff members per site (n=48) to complete a KII at baseline and 12 months. Eligible staff members are aged ≥18 years and work for 1 of the TG-DSD sites or a selected SSD site. We enroll 1 person in each role at each site, that is, peer navigator, community liaison officer, social worker, community health worker, nurse, and site manager. If a staff member leaves between baseline and 12 months, we will interview another person in the same role for the 12-month time point. We contact potential key informants via email or WhatsApp and invite them to participate.

An experienced qualitative researcher conducts the KIIs after the informed consent process. A semistructured KII guide will be used to organize the interview. KIIs last approximately 60 minutes and include open-ended questions that explore facilitators, barriers, strengths, and weaknesses of the DSD and SSD approaches and recommendations for improving service delivery. At the end of the qualitative interview, participants complete a brief, interviewer-administered quantitative tool measuring antitransgender stigma [71] and validated measures of intervention acceptability, feasibility, and appropriateness [72,73]. KIIs are audio-recorded with permission of the participant, and notes are taken during and after the interview to facilitate accuracy and appropriate analysis. Where possible, interviewers are fluent in local languages. When interpretation is required, a trained study staff member interprets during the interview.

We collect data on the costs of implementation at all TG-DSD sites by conducting a bottom-up analysis of the resources used and costs accrued by all transgender cohort participants who receive TG-DSD. We also collect facility-level data on overhead cost items, such as space, administration, and utility costs, and allocate these to the service and our cohort based on the number of visits. We use our extensive database of public sector prices and salaries, as well as information on staff levels at each site, to estimate the public sector costs; these are data we have used in other costing studies in South Africa [53,74,75].

In collaboration with local transgender organizations, trained transgender people recruit their peers from their social networks via social media posts, WhatsApp groups, and word-of-mouth. Eligibility criteria include age ≥18 years, identity as a gender different from the sex assigned at birth, and residence in the catchment area for 1 of the enrolled health facilities. Participants must either be living with HIV and prescribed ART or HIV negative and PrEP eligible (whether or not they are currently taking PrEP). We use stratified sampling to ensure enrollment of ≥400 participants on ART and ≥200 participants who are HIV negative. Within those strata, we further ensure that half are individuals who receive care at a TG-DSD site and the other half are transgender people who receive care at an SSD site in the same catchment area. We use quotas to ensure that no TG-DSD site makes up <20% of TG-DSD participants. At the enrollment visit, participants are rescreened for eligibility, including rapid HIV testing to confirm self-reported HIV status.

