## Methods

### Overall Study Design

Jabula Uzibone is an observational, multisite, mixed methods, and prospective implementation study. To meet the first aim, we will assess the implementation of TG-DSD models and SSD models at the facility level using standardized observation checklists at 8 facilities (1 DSD site and 1 SSD site per area in all 4 areas). We will examine implementation, acceptability, feasibility, and barriers to and facilitators of TG-DSD via key informant interviews (KIIs; n=6 per site) with health facility staff. At the client level, we will conduct in-depth interviews (IDIs) with 30 transgender people (15, 50% from DSD sites and 15, 50% from SSD sites) drawn from the longitudinal cohort enrolled for aim 2 described in the next paragraph.

To meet the second aim, we will enroll a cohort of ≥600 transgender people and follow them for 12 months. Of the transgender people enrolled, ≥400 (66.7%) will be transgender people living with HIV. This will include ≥200 (50%) who receive ART at TG-DSD sites and ≥200 (50%) who receive ART at SSD sites in the same area as the TG-DSD sites. We will also enroll ≥200 transgender people without HIV. This will include ≥100 (50%) participants without HIV at TG-DSD sites and ≥100 (50%) without HIV at SSD sites in the same area as the TG-DSD sites. Each participant will complete a quarterly survey to assess engagement in HIV prevention and care, changes over time in experiences of gender affirmation, and experiences of stigma.

For participants on ART, we will measure HIV RNA levels (ie, viral load) at baseline and 12 months. For participants on PrEP, we will measure tenofovir levels at baseline and 12 months. For participants who are HIV negative and not on PrEP, we will assess self-reported condomless sex. Prevention-effective adherence is defined as being HIV negative and meeting one of the following criteria: (1) adherent to PrEP based on tenofovir levels, (2) self-report of consistent condom use in the prior 30 days, or (3) self-report of no anal or vaginal sex in the prior 30 days. Table 1 presents a list of data collection activities organized by level of analysis, participant type, and month of enrollment.

**Table 1 table1:** Data collection activities by level of analysis, participant type, and month of enrollment.

Level			Participant, n (%)		Baseline		Months 3, 6, and 9		Month 12

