	**Client**			
		IDIs with transgender participants	Tell me about your experience receiving care at the site.	
		Survey with transgender participants	Intersectional stigma scale by Scheim and Bauer [77], Psychological Gender Affirmation scale by Sevelius et al [78], and GAHT use by self-report.	
		Laboratory test with transgender participants	HIV RNA level by serum analysis (for transgender participants on ART) and tenofovir level by DBS^i^ (for transgender participants on PrEP)	

^a^GAHT: gender-affirming hormone therapy.

^b^ART: antiretroviral therapy.

^c^PrEP: pre-exposure prophylaxis.

^d^KII: key informant interview.

^e^AIM: Acceptability of Intervention Measure.

^f^IAM: Intervention Appropriateness Measure.

^g^FIM: feasibility of intervention measure.

^h^IDI: in-depth interview.

^i^DBS: dried blood spot.

Qualitative interview (KII and IDI) recordings will be transcribed and translated into English. The transcripts, field notes, and narrative summaries will be uploaded into qualitative data management software, Atlas.ti (ATLAS.ti Scientific Software Development GmbH), to facilitate analyses. During regularly scheduled meetings, the study team will review field notes, transcripts, and summaries; discuss emerging themes; and revise interviewing and coding strategies, as needed.

Statistical analysis of quantitative data will be performed using Stata (StataCorp) and MPlus (Muthén & Muthén). Data exploration of key variables will be conducted to assess for implausible values and determine whether statistical assumptions (eg, normal distributions of data) for planned statistical analyses are satisfied. Categorical variables will be reported as frequencies and percentages, with means and SDs or medians and IQRs reported for continuous variables. Patterns of missing data will be examined, including testing for differences between participants with and without missing data. A series of sensitivity analyses will be conducted to evaluate the robustness of conclusions drawn from the primary models to departures from the missing at random assumption by comparing the magnitude of the primary effect. In the rare situation that >10% missing data is observed, we will use multiple imputation, as appropriate. We will specify 2-sided tests, .05 significance level (α=.05), and compute 95% CIs throughout.

### Qualitative Data Analysis for Aim 1

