We will use quantitative methods to evaluate the effectiveness of TG-DSD for viral suppression and prevention-effective adherence and to assess stigma and GAHT use as potential mediators. As noted earlier, our first hypothesis is that rates of viral suppression are more likely to increase among transgender people on ART at TG-DSD sites than among transgender people on ART at SSD sites over the 12-month study period.

The primary outcome measure is the proportion of transgender people on ART with viral suppression (HIV RNA <50 copies/mL). Descriptive analyses will summarize HIV viral suppression comparing participants at TG-DSD versus SSD sites as well as by gender identity at baseline and 12 months. Percent distributions will be computed for categorical variables and means, ranges, SDs, medians, and IQRs will be presented for continuous variables stratified by attendance at TG-DSD versus SSD sites. The primary estimate for this aim is the absolute difference in the change in proportion of virally suppressed during the study period between participants at TG-DSD sites and those at SSD sites. A difference-in-difference (D-i-D) analysis will be conducted to account for anticipated differences between groups at baseline (TG-DSD vs SSD). In addition, we will compare differences at 12 months considering baseline values to enhance the robustness of the estimators of the differences in the 2 groups.

A mixed-effects binomial model will be fit, where the binary viral load suppression status of each client is regressed on fixed effects for time (baseline vs 12 months), TG-DSD versus SSD site, the time by site model interaction, and client-level covariates (age and gender identity). In addition, random intercepts for each of the sites will be included in the model to account for within-site correlation. The D-i-D estimator is the estimated regression coefficient for the time by service delivery model interaction term. All models will account for clustering and be adjusted for relevant confounders in baseline covariates.

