### Statistical Power

Power analyses and sample size calculations were based on the primary outcome of viral suppression (aim 2). No viral load data are available for transgender people in South Africa disaggregated from other key populations. The only South African data that includes transgender women and uses the current nationally recommended threshold for viral suppression includes cisgender men who have sex with men. Nonetheless, the study found a viral suppression rate of 47% [101]. One study of transgender people receiving TG-DSD in South Africa found that those on GAHT were 3 times more likely to be virally suppressed compared to transgender people who are not on GAHT [49]. This suggests an effect size of at least 20%. We consider an effect size as low as 15% to be clinically significant.

On the basis of the aforementioned data and clinical experience, we anticipate that current viral suppression rates will be approximately 65% at baseline, rising to 85% at 12 months among TG-DSD participants, and approximately 61% at baseline, rising to 66% at 12 months among SSD participants. This 20% difference from baseline to 12 months for TG-DSD participants and 5% difference from baseline to 12 months for SSD participants represents a difference in the absolute change in viral suppression rates of 15%. Using *r*=1, α=.05, power of 1− β=.80, and p_1_=viral suppression in the SSD and p_2_=viral suppression in the TG-DSD group and difference of p_2_ – p_1_=.15, the minimum sample per group will be 172 for both TG-DSD and SSD, for a total minimum sample size of 344. Adjusting for loss to follow-up of approximately 12%, a sample of ≥200 in each group, for a total of ≥400 transgender people on ART, provides adequate statistical power for planned analyses.

Loss to follow-up is a challenge for any longitudinal study. We will make every effort to minimize loss to follow-up by collecting multiple forms of contact, reaching out monthly to update contacts, collecting data in the field as well as the study site, and providing remuneration for study participation. We are enrolling a larger sample size than required by the power calculations to allow for potential loss to follow-up without loss of statistical power.

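### The primary difference-in-difference model has no area-by-time term, so area-specific trends bias it whenever the two arms have different area mixes

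*Protocol article*

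**What the plan says.** **Pairing.** Under Overall Study Design, the eight facilities are "1 DSD site and 1 SSD site per area in all 4 areas". The facility-level part of Study Procedures adds that each SSD site lies in the catchment of its TG-DSD site and resembles it in urbanicity, client socioeconomic status and HIV services.

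**Sampling.** The same part of Study Procedures stratifies by HIV status (at least 400 on ART, at least 200 HIV negative). Within strata, "half are individuals who receive care at a TG-DSD site and the other half are transgender people who receive care at an SSD site"; the sentence then places that SSD site in the same catchment. The next sentence is the only site-level floor: "We use quotas to ensure that no TG-DSD site makes up <20% of TG-DSD participants". Its denominator is all TG-DSD participants. No floor is stated for SSD sites or within an HIV stratum.

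**Model.** Data Analysis for Aim 2 lists the fixed effects: time, service model, their interaction, age and gender identity. It then says that "random intercepts for each of the sites will be included in the model to account for within-site correlation". The interaction coefficient is the estimator. Unlisted baseline confounders will also be adjusted for. H2 follows the same steps.

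**Switching.** Data Analysis for Aim 2 censors participants who move from an SSD to a TG-DSD site. The reverse move is not mentioned.

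**Fallback.** The exploratory-analysis section allows inverse probability of treatment weighting if the groups differ on important characteristics. Area is not named there.

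**The concern.** A same-area comparator protects against local events over the year (supply, staffing, local programs) that move suppression in both clinics of an area. In the analysis, the protection works only if the arms have the same area mix or the model compares service types within area.

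The listed model does not make the comparison within area. A random site intercept absorbs a stable difference in level between sites, and so would a main effect of area. Neither absorbs a difference in change over time, and change over time is what the interaction term estimates. If one area improves more than the others and is more heavily represented in the TG-DSD arm, its improvement is partly credited to TG-DSD; with the reverse mix, a real effect is partly hidden.

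**Working it through.** **The plan's own figures.** The target is (85 − 65) − (66 − 61) = 20 − 5 = 15 points (Statistical Power). The stated 172 per group is reproduced by a two-proportion formula with pooled variance, two-sided α = 0.05 and power 0.80, if p1 is taken as the cited 47% and p2 as 62%:

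n = [1.960 × √(2 × 0.545 × 0.455) + 0.842 × √(0.47 × 0.53 + 0.62 × 0.38)]² / 0.15² = 171.8, so 172.

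The plan does not state which p1 it used. This point does not change the sample size; the 15 points serve only as the yardstick.

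**What the floor permits.** With 300 TG-DSD participants (200 on ART, 100 HIV negative):
- Floor per site: 0.20 × 300 = 60. Maximum for one site: 300 − 3 × 60 = 120, or 40%.
- In the ART stratum the floor does not bind, because 60 is below the 100 HIV-negative places. Example: site totals 120/60/60/60 with 120/40/20/20 on ART satisfy the floor and put 120/200 = 60% of the ART stratum at one site.

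**Bias formula.** With no TG-DSD effect, the expected difference-in-difference on the risk-difference scale is the sum over areas of (TG-DSD share − SSD share) × area change. If one area has an extra rise d and the others share a common trend, this is (TG-DSD share − SSD share in that area) × d.

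The documents give neither SSD shares nor area trends, so both are assumptions:

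| TG-DSD vs SSD share in the trending area | d = 5 points | d = 10 points | d = 20 points |
|---|---|---|---|
| equal | 0 | 0 | 0 |
| 40% vs 25% | 0.75 | 1.5 | 3.0 |
| 40% vs 10% | 1.5 | 3.0 | 6.0 |
| 60% vs 10% | 2.5 | 5.0 | 10.0 |

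**If enrollment is matched by area.** Suppose both arms start with 25% in each area and switching occurs only in the trending area. If half of its SSD participants are censored (assumption), its SSD share falls to 12.5/87.5 = 14.3%, and with d = 10 the bias is (0.25 − 0.143) × 10 = 1.1 points. The range is 0 if nobody switches to 2.5 points if all do.

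**Simulation with no true effect.** 176 per arm (200 × 0.88), 4,000 runs, assumed latent within-person correlation 0.5, and a linear change-score approximation to the planned mixed model:

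| Shares | d | Rejection, no area terms | Rejection, area-by-time | SE without → with |
|---|---|---|---|---|
| equal | 10 | 5.0% | 5.2% | 0.0585 → 0.0582 |
| 40/25 | 10 | 5.5% | 5.0% | 0.0584 → 0.0589 |
| 40/10 | 10 | 7.8% | 5.6% | 0.0584 → 0.0620 |
| 60/10 | 10 | 14% | 5.3% | 0.0580 → 0.0684 |
| 40/25 | 20 | 8.2% | 5.2% | 0.0582 → 0.0581 |
| 40/10 | 20 | 18% | 5.1% | 0.0582 → 0.0613 |
| 60/10 | 20 | 40% | 5.6% | 0.0576 → 0.0673 |

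With area-by-time terms the simulated bias is about 0 in every case. For d = 0 to 20, the standard error rises by about 5% to 7% for 40/10 and 17% to 18% for 60/10.

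**The case against.** The strongest reply is that the sampling sentence just before the quota already balances the arms. Read as 1:1 matching by catchment within each HIV stratum, it carries the TG-DSD floor over to the SSD side and makes the bias nil at enrollment. This reading is natural and may be what is meant. However, Overall Study Design gives arm totals only and describes the SSD sites collectively as lying in the areas of the TG-DSD sites, so the words may merely say where the SSD sites are. Matching at enrollment also does not settle the mix at month 12, since censoring runs in one direction. Two TG-DSD sites stand on SSD campuses and two stand alone, so switching could differ by area.

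Second, a reader might infer that the areas are shown to have different trends, because they differ in urbanicity and because HIV prevalence is 46% in two cities and 63% in a third. The documents do not support this. These are differences in level, which site intercepts handle, and prevalence is not suppression among people on ART. No area trend in suppression is reported.

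Third, a reader might infer that the sampling is unbalanced, that the pairing goes unused, or that a TG-DSD site may contribute nobody to H1. The pairing is used to choose SSD sites and perhaps to sample. A site with no ART clients is arithmetically allowed, but nothing suggests it: 348 of the 593 enrolled by July 31, 2024 were living with HIV.

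Fourth, other safeguards exist, and a condensed article may leave their detail to a fuller plan. That is fair for the covariate list. But baseline covariates entered as main effects do not remove area-specific change, and weighting would do so only if it were triggered and included area. Exploratory fits by facility cannot help, since each facility has one service model.

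**Conclusion.** The point holds as a conditional weakness of the specified model. Bias needs two things together: a different area mix in the two arms, at enrollment or by month 12, and a different 12-month change between areas. The documents establish neither, and they do not clearly exclude either.

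Under an assumed 10-point extra trend in one area, the bias runs from 1.5 points (40% vs 25%) to 5 points (60% vs 10%), that is 10% to 33% of the 15-point target. Reaching 10 points takes both a 20-point area trend and a 60% vs 10% split. With equal mix it is zero. The false-positive rates rest on the same assumptions and on the change-score approximation. The same mechanism applies to H2, for which the protocol gives no target effect. It is a moderate risk that can be removed cheaply.

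**What to change.** - Add area (4 levels) and area-by-time as fixed effects in the H1 and H2 difference-in-difference models, so that the service models are compared within area.
- Report participants by area, arm and HIV stratum at baseline and at month 12.
- State whether the 1:1 sampling is done area by area within each HIV stratum.

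**Cost.** Six extra parameters (3 for area, 3 for area-by-time) on data already held. In the simulation the standard error rises by about 5% to 7% for a 40/10 split and 17% to 18% for a 60/10 split; with equal mix it hardly changes. The terms remove change shared by both sites of an area, not change peculiar to one site.

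A change to the quota is not proposed. By July 31, 2024, 593 people were enrolled, the HIV-negative stratum (245) had passed its target of 200, 400 − 348 = 52 places remained in the HIV stratum, and enrollment was expected to end a month later.
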